## Abstract

**Background:**

Few data exist on the use of text messaging as a tool to promote retention in HIV care and virologic suppression at the clinic level in the United States. We describe the protocol for a study designed to investigate whether a text messaging intervention that supports healthy behaviors, encourages consistent engagement with care, and promotes antiretroviral persistence can improve retention in care and virologic suppression among patients in an urban safety-net HIV clinic in San Francisco.

**Methods/Design:**

Connect4Care (C4C) is a single-site, randomized year-long study of text message appointment reminders vs. text message appointment reminders plus thrice-weekly supportive, informational, and motivational text messages. Eligible consenting patients are allocated 1:1 to the two arms within strata defined by HIV diagnosis within the past 12 months (i.e. “newly diagnosed”) vs. earlier. Study participants must receive primary care at the San Francisco General Hospital HIV clinic, speak English, possess a cell phone and be willing to send/receive up to 25 text messages per month, a have viral load >200 copies/μL, and be either new to the clinic or have a history of poor retention. The primary efficacy outcome is virologic suppression at 12 months and the key secondary outcome, which will also be examined as a mediator of the primary outcome, is retention in HIV care, as operationalized by kept and missed primary care visits. Process outcomes include text message response rate and percent of time in study without cell phone service. Generalized estimating equation log-binomial models will be used for intent to treat, per protocol, and mediation analyses. An assessment of the cost and cost-effectiveness of the intervention is planned along with a qualitative evaluation of the intervention.

**Discussion:**

Findings from this study will provide valuable information about the use of behavioral-theory based text messaging to promote retention in HIV care and virologic suppression, further elucidate the challenges of using texting technology with marginalized urban populations, and help guide the development of new mobile health strategies to improve HIV care cascade outcomes.

**Trial registration:**

NCT01917994

**Electronic supplementary material:**

The online version of this article (doi:10.1186/s12879-014-0718-6) contains supplementary material, which is available to authorized users.

## Background

Retention in care is a key step in the HIV treatment cascade, the aim of which is to ensure that all individuals living with HIV are successfully treated [1]. Missed primary care visits have been associated with longer time to antiretroviral initiation and shorter time to virologic failure and death [2]-[4]. In addition to the timely management of HIV infection, regular visit attendance allows other important interventions to occur, such as risk reduction counseling, mental health and substance use referrals, and health care maintenance [5],[6]. Despite the proven health and prevention benefits of consistent HIV care, only about half of individuals living with HIV in the United States are estimated to be retained in care and only one-quarter are virologically suppressed [7].

Reasons for poor retention in HIV care are diverse and span individual (e.g. depression, stigma), interpersonal (e.g. patient-provider relationship), and structural (e.g. insurance eligibility) factors [8]. Evidence-based interventions to promote retention in care and virologic suppression include adherence counseling, medical case management, intensive outreach, and peer or paraprofessional patient navigation [9]. In addition, studies have shown that prompts and reminders are effective tools for both antiretroviral and appointment adherence [10]-[12]. Moreover, the randomized, multi-site Centers for Disease Control (CDC) Retention in Care project, demonstrated that patients receiving enhanced personal contact in addition to usual clinic practice exhibited a significant improvement in appointment attendance [13].

Short message service (SMS) technology represents a promising new strategy for HIV care. SMS has been deployed successfully in support of antiretroviral adherence and virologic suppression in sub-Saharan Africa and is currently being studied in this setting with regard to retention in care [14]-[16]. In the U.S., studies to date of text messaging in HIV-infected populations have generally focused on sub-groups, such as youth, substance users, and men who have sex with men [17]-[20]. Few studies to date have examined the impact of SMS on improving retention in care and virologic suppression for broader populations of marginalized persons using safety-net HIV clinics in the U.S. In a feasibility study of 25 patients receiving SMS appointment reminders in a Southeastern U.S. clinic, challenges to receiving SMS included discomfort with cell phone use, patients not opting in to receive messages, and service interruptions [21]. It is currently unknown whether such challenges are surmountable and whether a more comprehensive SMS intervention that supports healthy behaviors, encourages consistent engagement with health care, and promotes antiretroviral persistence would significantly influence virologic suppression among marginalized patients in the U.S. In addition, examining the cost of such an intervention is an important consideration for real-world feasibility.

Connect4Care (C4C) is a randomized controlled trial (RCT) examining the efficacy of a SMS intervention to improve virologic suppression and retention in care among patients at a safety-net HIV clinic in San Francisco. The C4C SMS intervention is designed to provide information about resources for healthy living, promote intrinsic motivation for engaging in HIV care, and support enhanced psychological adjustment. This integrative approach is based on: 1) several behavioral models commonly used to understand barriers and facilitators to engagement in care [22]-[26], and; 2) a conceptual framework designed to integrate the communication functionality of SMS with psychosocial factors known to impact health outcomes [27]. C4C builds on the existing evidence base for SMS interventions that have been conducted in resource-limited settings by providing empirical data to examine SMS influences on disadvantaged individuals living in a resource-rich environment. This paper describes the C4C study protocol.

### Study objectives

#### Primary objective

To determine whether the C4C intervention improves virologic suppression at 12 months when compared to SMS appointment reminders alone.

#### Key secondary objectives

To determine whether the C4C intervention improves retention in clinic care at 12 months, as operationalized by measures of kept and missed primary care visits.

#### Other secondary objectives

1) To determine the effect of the C4C intervention on psychosocial outcomes, including reduced depressive symptomatology as well as increased positive affect, social support, health-related quality of life, and health care empowerment. 2) To assess the cost of intervention delivery and cost-effectiveness of the C4C intervention. 3) To explore participant experiences with the C4C intervention as well as barriers to and facilitators of the use of SMS technology through a qualitative sub-study.

## Methods

### Study design

C4C is a single site, parallel arm, open-label RCT of SMS appointment reminders alone vs. SMS appointment reminders plus thrice-weekly SMS messages that deliver information and enhance motivation and psychosocial adjustment. Eligible consenting patients are allocated 1:1 to the two arms within strata defined by HIV diagnosis within the past 12 months (i.e. “newly diagnosed”) vs. earlier (Figure 1).

**Figure 1 Fig1:**
[figure not shown]
**C4C flow diagram.**

### Study settings

The HIV clinic at San Francisco General Hospital (SFGH), also known as Ward 86, is one of the oldest and largest public HIV clinics in the United States, serving 3,000 low-income patients as part of San Francisco County’s safety-net hospital. Patients at Ward 86 represent multiple urban populations, including the recently incarcerated, substance users, homeless and unstably housed individuals, and those with mental illness. Approximately 12% of clinic patients are women, 25% are African-American and 20% are Hispanic/Latino. Consistent with national guidelines, the clinic standard of care is to offer antiretroviral therapy to all individuals, irrespective of CD4 cell count [28]. The clinic standard of care is also to provide reminder phone calls to patients at least 2 days prior to primary care appointments, however, the consistency of this practice is dependent on staffing levels. Patients are screened for eligibility in the clinic, but baseline, 6, and 12-month study visits take place at a clinical research site in the community. This separate study site minimizes the likelihood that participation in the study influences the key secondary outcome of retention in clinic care.

### Study participants

The study sample consists of HIV-infected individuals age 18 or older who receive primary care at Ward 86, speak English, have a cell phone, can read a text message, and are willing to send or receive anywhere from 1 to 25 text messages per month. In addition, participants must have detectable viral loads (>200 copies/μL) and be either: 1) new to clinic (defined as no more than 2 primary care visits at Ward 86) or 2) have a history of poor retention (defined as one or more missed visits or lack of six-month visit constancy in the past 12 months at Ward 86).

### Inclusion criteria

HIV-infectedAge 18 or olderEnglish-speakingAble to give informed consentHave a cell phone, can read a text message, and willing to send/receive up to 25 text messages per monthViral load >200 copies/μL within past 4 weeks and either: 1) new to clinic (no more than 2 primary care visits at Ward 86) or 2) history of poor retention (one or more missed visits at Ward 86 or lack of six-month visit constancy in the past 12 months).

### Exclusion criteria

Under age 18Non English-speakingUnable to give informed consentViral load <200 copies/μLNo missed visits and achievement of six-month visit constancy in the past 12 months in an individual whose viral load is >200 copies μL

#### SMS interactions with participants

Information on pending primary care appointments is downloaded from the hospital electronic medical record and transmitted automatically to a text messaging platform that sends SMS reminders two days prior to HIV primary care appointments. All study participants receive reminders stating, “You have an appointment on Tuesday, June 18th, at 11:30 am with your provider at SFGH, Building 80, 6th floor. Please call XXX-XXX-XXXX to cancel or reschedule”. Participants choose morning or afternoon times during business hours to receive appointment reminders, so that they can call the clinic to reschedule if they are unable to make the appointment.

All participants also receive a monthly text message that reads, “This is your monthly check in from C4C. Thanks for your participation. Please respond C to confirm you received this message”. If participants do not respond to the monthly check-in message, a research assistant calls the participant to ensure that the phone is working and contact information is up to date, unless the participant is in the intervention arm and noted to have responded to an intervention message in the week before or after the check-in message (see *C4C Intervention* below). The monthly check-in message was designed to promote study retention among control arm participants and to track their length of follow-up in the study, as some participants may only have primary care appointments scheduled every three to four months.

Participants are counseled on the potential for bugs and glitches in the SMS system and informed that it is not a method for communicating with study staff or with the clinic. A reply to any study SMS that does not ask for response, including the SMS appointment reminders, results in the message, “Thanks for the feedback. If this is an emergency, please call 911”. At the enrollment visit, a research assistant programs the number from which text messages are sent into the participant’s phone as “C4C Study”.

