#### Control condition

The control condition includes only the SMS appointment reminders and the monthly check-in messages.

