### Process outcomes

Response rate to monthly check-in “blast”Response rate to Type 2 and 3 intervention messagesPercentage of time in study without cell phone service

As is true of many randomized trials, C4C exists on the continuum between efficacy and effectiveness [37]. Efficacy studies determine whether an intervention produces the expected result under ideal circumstances and effectiveness studies measure the degree of beneficial effect in “real world” settings [38]. C4C only enrolls patients who are in clinical care and willing to participate in a research study, potentially resulting in a less generalizable sample that is more consistent with an efficacy study. However, it does not provide participants with cell phones or airtime, which acknowledges that service interruptions (and thus interruptions in the intervention) represent “real world” implementation. This study decision was based on an emerging area of importance in behavioral (non-pharmacologic) interventions [39] and text messaging studies in particular [40] – that of process evaluation, which seeks to determine whether the intervention was delivered as intended and whether participants engage with the intervention.

Participants may experience disruption in receiving SMS appointment reminders and intervention messages due to cell phones being lost or stolen, participants’ inability to pay their bills, or participant loss to follow-up. We therefore plan to track the frequency of responses to monthly check-ins for all participants and for Type 2 and 3 messages in the intervention arm. We will also record self-reported loss of phone access at study check-ins by phone and at in-person study visits.

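### Only intervention participants can be excused the staff call after a missed monthly check-in, which risks unequal staff contact and possible dilution of the effect

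*Protocol article*

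**What the plan says.** All references are to the protocol article.

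- **SMS interactions with participants.** Both arms receive the monthly check-in. "If participants do not respond to the monthly check-in message, a research assistant calls the participant", with the stated aim "to ensure that the phone is working and contact information is up to date". The one exemption reads "unless the participant is in the intervention arm and noted to have responded to an intervention message in the week before or after", counted from the date of the check-in. The check-in itself has a purpose centred on one arm: "The monthly check-in message was designed to promote study retention among control arm participants and to track their length of follow-up in the study".
- **Control condition.** "The control condition includes only the SMS appointment reminders and the monthly check-in messages". The calls are not mentioned. The C4C intervention section does not mention them either.
- **C4C intervention.** Intervention participants get at least one message a week that asks for a reply.
- **Follow-up of study participants.** Calls at 3 and 9 months are described without distinction by arm. Study visits are held away from the clinic so that the study does not affect clinic attendance. Study settings gives the same reason.
- **Blinding.** Staff know the allocation.
- **Background.** A cited multi-site trial found that "patients receiving enhanced personal contact in addition to usual clinic practice exhibited a significant improvement in appointment attendance".
- **Process outcomes.** "We will also record self-reported loss of phone access at study check-ins by phone and at in-person study visits".

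**The concern.** Two participants with the same missed check-in are handled differently because of their arm. The control participant is always called. The intervention participant may not be. A control participant who texted back after an appointment reminder has also shown that the phone works, but has no exemption.

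Attendance is the key secondary outcome, and it is also to be examined as a mediator of suppression. The plan moves study visits off the clinic site so that study contact does not affect attendance, and it cites evidence that personal contact can improve attendance. An arm-dependent call rule works against that precaution. If the calls help at all and go mainly to controls, the contrast between arms shrinks. More frequent updating of control contact details could also make tracing of lost participants unequal, in a direction that cannot be predicted.

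**Working it through.** **The plan's own figure.** Inputs from Sample size: 60% against 75%, 80% power, two-sided α = 0.05, 1:1 allocation. With the pooled-variance formula and no continuity correction:

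n = [1.960·√(2·0.675·0.325) + 0.842·√(0.60·0.40 + 0.75·0.25)]² / 0.15² = 152 per arm.

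This matches the stated 152.

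**Expected calls.** There are 12 monthly check-ins in the year. Let q be the probability of not answering one. Let r be the probability that an intervention non-responder replied to an intervention message in the week before or after. The document gives neither, so both are assumed over a range. The two-week window normally holds at least two messages asking for a reply, so r need not be small.

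- Control: 12q
- Intervention: 12q(1 − r)
- Difference at equal q: 12qr

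| q | r | Control | Intervention | Difference |
|---|---|---|---|---|
| 0.1 | 0.3 | 1.2 | 0.84 | 0.36 |
| 0.1 | 0.5 | 1.2 | 0.60 | 0.60 |
| 0.1 | 0.8 | 1.2 | 0.24 | 0.96 |
| 0.3 | 0.3 | 3.6 | 2.52 | 1.08 |
| 0.3 | 0.5 | 3.6 | 1.80 | 1.80 |
| 0.3 | 0.8 | 3.6 | 0.72 | 2.88 |
| 0.5 | 0.3 | 6.0 | 4.20 | 1.80 |
| 0.5 | 0.5 | 6.0 | 3.00 | 3.00 |
| 0.5 | 0.8 | 6.0 | 1.20 | 4.80 |

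These are calls triggered per person-year. A call to a lost or disconnected phone may reach nobody.

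**When the order reverses.** If non-response differs by arm, the counts are equal when q_I(1 − r) = q_C, that is, q_I / q_C = 1/(1 − r). This ratio is 1.43 for r = 0.3, 2 for r = 0.5 and 5 for r = 0.8. Above it, the intervention arm gets more calls. Because q_I cannot exceed 1, reversal is possible only if q_C is below 1 − r. For example, at r = 0.5 and q_C = 0.3, q_I would have to exceed 0.6.

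**What dilution would cost, for scale only.** Suppose the extra calls raised control suppression by s points while the intervention arm stayed at 75%. Power at 152 per arm would be:

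| s (points) | Power |
|---|---|
| 0 | 80.0% |
| 1 | 74.7% |
| 2 | 68.6% |
| 3 | 62.0% |

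Nothing in the document links a number of calls to any value of s. The table shows only how sensitive the design is.

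**The case against.** The case for leaving the rule alone has several parts.

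- **The exemption has a rationale.** A reply within a week of the check-in shows that the phone works, which is most of what the call is meant to establish. Intervention participants without such a reply are called like controls. This stands, and it weakens any argument that controls alone are helped to keep receiving reminders. It does not remove the difference in live staff contact.
- **The calls are slight.** They are administrative checks with no stated counselling content, and both arms also get calls at 3 and 9 months. The evidence in Background concerns enhanced contact and attendance, not brief phone checks or viral load. This stands, and it is why no size can be put on the effect.
- **More calls to controls is not established.** A reader might infer that controls do receive more contact. That needs non-response by arm, which is not given, and people receiving three extra texts a week may skip check-ins more often.
- **Controls called sooner.** A reader might infer this from the week-after condition. No call timing is stated for either arm, and a reply in the week before triggers the exemption without any wait.
- **Phone-service data sampled unequally.** A reader might infer this from Process outcomes. The wording there may refer only to the 3- and 9-month calls, which do not differ by arm. The point holds only if phone loss is also recorded at the non-response calls.
- **Control condition is not a contradiction.** It can be read as a list of message content, with the calls as follow-up monitoring in both arms. That is fair. Even so, neither description tells the reader that live calls occur on different rules.

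**Conclusion.** The point holds as a risk. The text itself makes the call rule depend on arm, and unblinded staff apply it. At similar check-in non-response, controls would receive 12qr more calls per person-year, or 0.36 to 4.8 over the assumed ranges. If those calls have any benefit, the likely consequence is dilution, more directly for retention in care than for virologic suppression.

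The document does not support the stronger conclusion that the comparison is biased toward no effect. Which arm gets more calls depends on non-response rates that are not stated, no effect of a call is given, and the size of any dilution cannot be computed. It is an avoidable inequality that is cheap to remove, not a demonstrated bias.

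**What to change.** 1. Use one trigger and one timing for both arms: call every participant who does not answer the monthly check-in, whatever other messages were answered. A neutrally worded exemption for a reply to any study text would not be equal, because the weekly messages that ask for a reply go only to the intervention arm.
2. Log staff calls per participant and report them by arm, including those made under the present rule.
3. Mention the calls in the Control condition and C4C intervention sections.
4. If phone loss is also recorded at these calls, base the between-arm comparison of phone service on the identically scheduled contacts at 3, 6, 9 and 12 months and on the failed-transmission logs already kept.

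The cost is 12qr extra calls per intervention participant-year by the existing research assistants, so a few at most over the ranges above. Some would go to participants already known to be reachable.

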#### Control condition

The control condition includes only the SMS appointment reminders and the monthly check-in messages.

#### C4C intervention

The C4C intervention is designed to foster a sense of connectedness to one’s health and health care as a means of promoting virologic suppression and retention in care. In addition to the monthly check-in messages and appointment reminders, it consists of motivational, informational, and supportive text messages three times per week over a period of one year, based on studies showing that daily messages are less effective than weekly or less than weekly messages [14],[29]. We used a conceptual SMS framework developed by Coomes et al. [27] and drew upon several behavioral models frequently used to understand engagement in HIV care to identify important theoretical constructs [27]. These models included the Behavioral Model for Vulnerable Populations, the Information, Motivation, and Behavior Skills model, the Health Care Empowerment model, and revised Stress and Coping Theory [22]-[26],[30]. As a team of HIV clinicians and behavioral scientists, we created intervention texts in six domains (Table 1) that targeted a sixth-grade reading level. To inform the development of the intervention messages, we conducted formative research with patients and clinic staff. We conducted three focus groups with clinic social workers, linkage team members, and current clinic patients to refine the intervention content.

